**Data collection and management**

Data collection- Routine data will be extracted from the ICU records; Study-specific outcome data will be collected every eigh^th^-hour Data collectors will be distinct from the persons administering the epidural morphine/ vs. placebo- (in this case, air)

Photographic evidence will be kept of ventilator parameters, USG of the diaphragm, and subjective comfort and dyspnea scores at each data collection point and sent from inside the COVID ICU to the investigator who is not involved in the patient's clinical care and unaware of group allocation via Whatsapp.

Data entry- Will be done from the photographs and paper Case Report Forms (CRFs) into an Excel sheet by a researcher blinded to the group allocation.

For each time point, representative photographs (de-identified) will be kept for possible crosschecking and data validation as required.

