**Respiratory Drive and related parameters**

Once at baseline and once every 8 hours after that, the following will be assessed till the epidural catheter is in situ, or five days whichever is greater.

The researcher will do the baseline assessment, be aware of the group allocation, and insert the epidural catheter (true or sham). She/ He will mark the site of best visualization for USG probe, ensure best fit NIV interface and assess baseline subjective comfort scores.

After that, all assessments will be done by a fixed set of postgraduate ICU trainees, all trained in TFDi assessment but blinded to group allocation.

Ultrasound-guided TFDi- This procedure will be performed as described earlier.(17,19)

The patient will be supine with head-end elevated to 30 %. The right hand will be abducted and kept near the head. The diaphragm will be located by placing the transducer in the intercostal space above the right 8^th^- 11^th^ intercostal space, in the anterior- axillary line, directing the ultrasound beam perpendicular to the diaphragm. The inferior border of the costophrenic sinus will be identified at end-inspiration as the zone of transition from the lung sliding shadow to the visualization of the diaphragm and liver. The zone of apposition will be noted.

The diaphragm thickness will be recorded in time motion (TM) mode.

The sweep speed will be adjusted to obtain a minimum of three to 8 cycles on the same image.

Several diaphragm images (outlined by the two clear, bright parallel lines of the pleural and peritoneal membranes) will be located: the image will be discarded if the two bright lines are not visible. The least and maximum thickness as on eyeballing will be located and a picture stored for subsequent quantitative analysis and crosschecking by a blinded assessor.

The position of the first (baseline) USG assessment will be marked on the skin to allow all subsequent recordings from the same position.

A note will be made of the ongoing sedation dosages and ventilator settings during the measurement of TFdi (settings will be kept the minimum required for patient comfort – but will not be changed/ dictated for purposes of the study)

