**Sample size**

Sample size justification A pilot study showed the mean TFDi in COVID 19 patients on PEEP 5 and clinically optimal pressure support to be 45% (SD 15); To decrease this by 30% at 36 hours after the dose of morphine with allocation in a 1:1 ratio, 21 patients will be needed in each group.

Compliance and missing data- All analyses will be based on the groups as randomly allocated: an intention-to-treat analysis. A per-protocol analysis will also be done. The statistical significance will be taken as the 5% level for the top comparisons and the subsidiary comparisons, the 1% level. Patients with a P/F ratio > 150 at inclusion will be compared to those with lower values.

Data Storage- Because of the unique challenges of repeated data capture in COVID ICU, all repetitive data will be captured photographically and sent to a central data repository online to be categorized and stored by patient name and time of data capture (once every 8 hours), making in 14-time points of data capture for each patient. Data storage will be by blinded personnel.

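### Photographs are called de-identified in one section but filed by patient name and time in another, and nothing shields the blinded reader of the diaphragm images from name, time point and the accompanying readings

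*Protocol*

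**What the plan says.** **What is photographed and who receives it.** Protocol, Data collection and management: "Photographic evidence will be kept of ventilator parameters, USG of the diaphragm, and subjective comfort and dyspnea scores at each data collection point". These pictures leave the COVID ICU by a messaging service and go to one investigator, described as outside the patient's care and unaware of allocation. Values from the photographs and paper forms are entered "into an Excel sheet by a researcher blinded to the group allocation". The section adds: "For each time point, representative photographs (de-identified) will be kept for possible crosschecking and data validation as required".

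**How it is filed.** Protocol, second Sample size section (under Detailed methodology), Data Storage paragraph: all repetitive data are captured photographically and "sent to a central data repository online to be categorized and stored by patient name and time of data capture". The paragraph counts 14 time points per patient and says that storage staff are blinded.

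**Who measures.** Protocol, Respiratory Drive and related parameters: the least and greatest diaphragm thickness are located by eye and "a picture stored for subsequent quantitative analysis and crosschecking by a blinded assessor". Assessments after baseline are made by trainees blinded to the group. The researcher who makes the baseline assessment knows the allocation and places the true or sham catheter.

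**Blinding in general.** Protocol, Outcome assessment: the assessor, the patient and the treating staff are blind to the group.

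**The concern.** A picture filed online under a patient's name is hard to call de-identified, so the two sections need to be reconciled for confidentiality alone.

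The statistical interest lies in the endpoint. TFdi is primary and comes from thickness measurements made by hand on a stored picture. The only filing order described links each patient's pictures by name and puts them in time order. The ventilator display (p0.1, rate, tidal volume, minute ventilation) and the comfort and dyspnea scores are photographed at the same moment and sent to the same place. The Introduction expects morphine to lower respiratory drive and dyspnea, and the Objectives list several of these readings as outcomes. Someone who sees them beside the diaphragm picture may form a view about the arm without ever seeing the code.

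If such a view influenced the measurements, the error would differ between the arms. A larger sample does not average out that kind of error.

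**Working it through.** **1. The identifier statements side by side**

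| Section | Material covered | Identifier |
|---|---|---|
| Data collection and management | representative photographs, each time point | none (de-identified) |
| Sample size, Data Storage | all repetitive data, captured photographically | patient name and time |

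The second row includes the diaphragm images, so the two rows overlap and disagree.

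**2. What the blinding statements cover**

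The receiving investigator, data entry, post-baseline bedside assessors, image assessor and storage staff are all said to be blinded. Each statement concerns the allocation. None says that the image reader works without the name, the time or the companion photographs, or in random order. Equally, none says that the reader is the person who receives the photographs, or that the reader opens the ventilator and comfort pictures. The protocol is silent in both directions.

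**3. The plan's own figure, for scale**

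Inputs from the Sample size sections: mean TFdi 45%, SD 15, 30% reduction, 1:1 allocation, 21 per group, 25 recruited. The target difference is 0.30 × 45 = 13.5 points. Power and sidedness are not stated; two-sided 5% and 80% are assumed.

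- Normal approximation: n = 2 × (1.960 + 0.842)² × 15² / 13.5² = 19.4, so 20 per group.
- t-test version (standardised difference 0.9): 20.39, so 21 per group.

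The stated 21 is reproduced, and it does not depend on this point. Reading the 30% as absolute points gives 4 to 7 per group, so 13.5 is the right yardstick.

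**4. Sensitivity of TFdi to caliper placement**

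TFdi = (max − min) / min. The documents give no diaphragm thickness, so end-expiratory values of 1.5, 2.0 and 2.5 mm are assumed. With a true TFdi of 45%, max = 1.45 × min.

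| min (mm) | max (mm) | min read 0.1 mm too high | max read 0.1 mm too low |
|---|---|---|---|
| 1.5 | 2.175 | 0.575/1.6 = 35.9% | 0.575/1.5 = 38.3% |
| 2.0 | 2.900 | 0.8/2.1 = 38.1% | 0.8/2.0 = 40.0% |
| 2.5 | 3.625 | 1.025/2.6 = 39.4% | 1.025/2.5 = 41.0% |

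The falls run from 4.0 points (45 − 41.0) to 9.1 points (45 − 35.9), which is 4.0/13.5 = 30% to 9.1/13.5 = 67% of the target difference.

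**5. What a reading bias would do if there were one (illustration only)**

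Assume no true effect, SD 15, 25 per arm and an unpaired t-test with 48 degrees of freedom at the final level of 0.04. A differential bias of b points gives a non-centrality of b / (15 × √(2/25)) = b / 4.24.

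| b (points) | 0 | 1 | 2 | 3 | 5 |
|---|---|---|---|---|---|
| False-positive rate, two-sided | 4.0% | 4.5% | 6.2% | 9.0% | 18.5% |

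The values of b are assumptions. Nothing in the protocol suggests which of them, if any, applies.

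**6. Workload of a recoding step**

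50 patients × 14 time points = 700 image sets at most. About half, 25 × 14 = 350, would be on hand by the interim analysis at 50% recruitment.

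**The case against.** A reader might infer that the primary endpoint is not read blind. The protocol does not support that. It states blinding for everyone who handles the data after baseline, a patient's name does not reveal the arm, and no text makes the recipient of the photographs the measurer of the images.

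Knowing the time point is also less informative than it seems. Both arms have a catheter, matching dressings and injections (air in controls), so pre-dose and post-dose pictures can be told apart in both. The primary comparison is between groups, and an expectation applied equally to both arms does not favour morphine. Only a guess at the arm would. Such a guess from rate or comfort is uncertain, because either arm may receive midazolam or dexmedetomidine and ventilator settings follow clinical need. This stands, although time alone could still colour the planned within-group comparisons.

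The caliper figures assume a full 0.1 mm shift, in one direction and different by arm. TFdi is an average of three readings, so isolated slips are diluted. This stands too: the figures show sensitivity, not bias.

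It can also be said that the pictures may be free of identifiers while only the folder carries the name. That softens the conflict but does not resolve it, since a reader who opens the folder sees the name.

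Finally, random reading order and custody of a key often belong in an imaging or data-management plan. Here, however, the protocol itself fixes the filing rule, so the rule can be judged and improved where it stands.

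**Conclusion.** The point holds in a limited form. The two sections contradict each other on whether the photographs carry an identifier. The protocol also does not say that the blinded assessor measures the diaphragm images without the name, the time point and the accompanying ventilator and comfort or dyspnea photographs. These are possible cues to the arm for a hand-measured primary endpoint.

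The size of any resulting bias is unknown. The sensitivity is a fall of 4 to 9 TFdi points per 0.1 mm of caliper shift, or 30% to 67% of the 13.5-point target, on assumed thicknesses of 1.5 to 2.5 mm. A differential bias of 3 points, if it existed, would raise the false-positive rate from 4% to about 9%. Neither figure shows that such a bias would occur, and the sample size is unaffected. This is a cheap improvement worth making, not evidence of an unblinded endpoint.

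**What to change.** In the Data Storage paragraph, replace filing by name and capture time with a trial code plus a random image code. Someone who does not read images should hold the key. Word the de-identification sentence in Data collection and management to match.

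Store diaphragm images apart from the ventilator and comfort or dyspnea photographs. Under Respiratory Drive and related parameters, state that the blinded assessor already named there measures the coded images in random order across patients and times, and that this measurement is the analysed TFdi. Read in batches, so that values are ready for the interim analysis.

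**Cost.** Up to about 700 image sets to split and recode, a key list, and a short delay before values are available. No new procedure and no added burden for patients.

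**Limit.** The change reduces exposure to cues but does not end it. The bedside trainees, who see the patient and the ventilator, still choose which frame is stored, and the baseline assessment is still made by a researcher who knows the allocation. Recoding files afterwards reaches neither.
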